## Discussion

This RCT seeks to test the effectiveness of a 4-min intervention video aimed at improving help-seeking for mental health difficulties among Australian men. The intervention video tested in this trial will form part of a larger media campaign aimed at improving help-seeking for mental health difficulties among Australian men.

This RCT will be conducted completely online. Our research team has designed this online trial to ensure it can be completed in the current Australian environment in which much of the population is in ‘lockdown’ due to the Covid-19 pandemic, prohibiting face-to-face interactions with participants and travel for data collection. Our methodology could be adopted for similar purposes with other interventions, but also applied to the development of media campaigns aimed at improving mental health outcomes in other countries or targeting other population groups (e.g. older people or those living in rural communities). Although our research team has conducted similar RCTs with media interventions, this is the first to make use of an online group orientation meeting. Securing the attendance of potential participants at this meeting is a potential challenge, as are the logistics of running such a group session online. However, with current (and possible future) insecurities around in-person group gatherings due to the risks posed by Covid-19, it is a useful RCT design and one that could be capitalised on in the future.

We recognise a number of potential biases to be introduced within this trial. While the RCT design attempts to control a number of these, we have also taken additional steps beyond the randomised double-blind design. One of the most likely biases is in participant selection. In our recruitment advertising, we have attempted to minimise the amount of specific information provided on the purpose of the study while providing enough information to allow participants to provide informed consent to participate. To wit, we have stated in the recruitment materials that the study is about men’s attitudes towards mental health and wellbeing. We recognise that this advertising is most likely to attract those with a particular interest in mental health who may not represent the broader population. However, we will attempt to minimise this selection bias by advertising through a range of channels that target men who do not necessarily have a high level of mental health literacy. For example, we will target university students studying in disciplines such as business and engineering rather than targeting those in the health or social sciences. We will also target a wide range of groups such as parenting and sporting groups and the networks of our film and advertising colleagues, who might have less exposure to mental health information than our networks.

We also recognise that, given the participants will meet at least one researcher in the online baseline data collection session, there is potential for social desirability bias. That is, that participants may be inclined to respond in the way they expect the researchers would prefer. We would expect this effect to be equal between intervention and control arms, particularly as the researchers are blind to participant allocation, but we have also chosen to use for the assessment of our primary outcome a change-in-change analysis. We will assess whether the intervention group shows a greater increase in help-seeking intentions than the control group, rather than a specified level of change within groups, thereby controlling for a consistent level of social desirability bias between the groups.

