#### Inclusion criteria

Aged 18 years or overIdentifies as maleResides in AustraliaUnderstands and reads English

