#### Exclusion criteria

Scored ≥ 2 on the DSI-SS [12], and the study psychologist determines that the participant is actively suicidal or likely to experience harm from further participation.

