### Procedure

#### Recruitment

Recruitment will occur online. To ensure participation from a broad cross-section of Australian men, we will use a variety of online recruitment methods. We will use our project partners (e.g. Gotcha4Life, a men’s suicide prevention organisation), and personal and professional networks to recruit participants, as well as public channels. We will send a recruitment flyer via email to researchers providing advice to the project, partners and own networks requesting they in turn share the recruitment information with their networks and via their mailing lists, websites and social media accounts, including Twitter, Instagram, Facebook and LinkedIn. We will post the recruitment information on the University of Melbourne student portal and in student newsletters aimed at departments with significant male enrolments such as Engineering, and Business and Commerce. We will also encourage snowballing (for those who participate to also recruit others).

Participants will be informed via the recruitment materials that the study relates to the attitudes of Australian men to mental health and wellbeing. We have chosen to present this aim of the study as it accurately orients participants to the context of the study without creating unnecessary bias by stating more specifically that we are examining the effects of a video on help-seeking intentions for mental health difficulties.

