##### Intervention

The intervention is a music video of approximately 4-min length created specifically for this study. It features a large group of diverse men singing a song in a community town hall. The song’s lyrics relate to the need for men to talk to others when experiencing mental health difficulties and to encourage others to do the same. The ‘call to action’ at the end of the video is ‘When the going gets tough. Get Talking’, and then there is a link to a website, which will provide links to further mental health support. This website will not be live during the trial to ensure that we can isolate any effects of the video from any effects of additional actions that might take place after participants watch the video.

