We have chosen the change in help-seeking intentions between T1 and T2 as our primary outcome for two main reasons. First, we expect that if there is an effect of this short intervention video, it will be immediate. We are encouraging men to seek help for mental health difficulties before they escalate. These sorts of difficulties are extremely common, and the help-seeking message is therefore likely to be immediately salient to most participants. We recognise that while intentions to seek help can change immediately, actual help-seeking may take longer. Therefore, we will assess help-seeking behaviour as a secondary outcome at T3 (1-month after baseline), as well as whether any increase in help-seeking intentions has been retained. Second, in the context of our collaboration with our film and advertising colleagues, we have created a broader campaign within which this video is at the core. The broad campaign will promote the video within the context of a range of other campaign materials promoting help-seeking. Within this trial, we want to be sure that the video does no harm to participants and ideally has a positive impact, but we also anticipate that by itself, this short video would be likely to have a short, sharp impact, while the broader campaign will have a greater, more lasting impact. We will do further empirical evaluation to test the impact of the broader campaign once it has been released. Therefore, the findings of this trial form a broader assessment of the campaign impacts that focus purely on the shorter-term effects of the video viewing.

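### Recruitment reaches into the networks of the colleagues who helped create the campaign, but nothing excludes or identifies men who took part in or have already seen the unreleased video

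*Protocol article*

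**What the plan says.** The Discussion, in its paragraph on selection bias, lists channels meant to reach men with less mental health literacy. Among them are "the networks of our film and advertising colleagues, who might have less exposure to mental health information than our networks".

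The Primary outcomes section describes those colleagues' role, referring to "our collaboration with our film and advertising colleagues, we have created a broader campaign within which this video is at the core". The Intervention section says the video was made for this study and describes its cast: "It features a large group of diverse men singing a song in a community town hall".

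The Recruitment section adds project partners and "personal and professional networks to recruit participants, as well as public channels", and encourages participants to recruit others.

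The inclusion criteria are, in full (line breaks lost in extraction), "Aged 18 years or overIdentifies as maleResides in AustraliaUnderstands and reads English". The only exclusion begins "Scored ≥ 2 on the DSI-SS [12], and the study psychologist determines that the participant is actively suicidal" and extends to likely harm from taking part. The T1 content in the Participant timeline and Table 1 has no item on prior knowledge of the video.

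Two safeguards depend on participants not knowing about the video. The Recruitment section withholds that a video's effect on help-seeking is being tested. The allocation section keeps participants unaware until T3 that there are two videos.

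**The concern.** An unreleased video is known mainly to the people who made it, appeared in it or were shown it. The plan recruits near that group and justifies the channel only by these men's lower exposure to mental health information. It does not consider that they may know more about this particular video.

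Three things follow for a man with prior exposure:

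- **Baseline.** His T1 score may already reflect the video.
- **Contrast.** If he is allocated to the intervention, a second viewing may add little, so his T1-to-T2 change understates the effect.
- **Masking.** On opening either link he can tell whether he has been sent the campaign video. The primary outcome is self-reported intention, which is open to such knowledge.

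The Discussion expects social desirability bias to be equal between arms and relies on comparing changes to cancel it. That comparison removes a bias common to both arms. It does not remove one that depends on which video the man recognises.

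**Working it through.** No figure in the plan is in dispute. The check sets the sections side by side and then gives a scale.

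**Text.** The channel is named (Discussion). The colleagues on that channel helped create the campaign (Primary outcomes). No criterion or listed T1 item removes or flags exposed men (Inclusion criteria, Exclusion criteria, Participant timeline, Table 1). Applied as written, a man who sang in the video is eligible and would be randomised.

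**Model of the primary contrast.** Let p be the share exposed before T1, equal in both arms in expectation because exposure precedes randomisation. Let δ be the effect of a first viewing, r the fraction of δ that an exposed man gains on viewing again, and b1 and b0 the reporting shifts from recognising one's arm (intervention, control). Measured relative to an unexposed control man, the mean T1-to-T2 changes are:

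- control, unexposed: 0
- control, exposed: b0
- intervention, unexposed: δ
- intervention, exposed: rδ + b1

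The between-arm contrast is therefore (1 − p)δ + p·r·δ + p(b1 − b0).

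The dilution comes only from the intervention arm. An exposed control man has a shifted baseline but no new exposure, so apart from b0 his expected change equals that of any other control man.

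**Dilution, worst case r = 0, with b1 = b0.** δ = 0.25 (Sample size section); p is assumed.

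- p = 2%: 0.25 × 0.98 = 0.245 (about 9 of 446 men)
- p = 5%: 0.25 × 0.95 = 0.2375 (about 22 men)
- p = 10%: 0.25 × 0.90 = 0.225 (about 45 men)

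**Power.** Inputs from the Sample size section: correlation 0.67, two-sided 5%, 223 per arm less 20% = 178.4 completers per arm. The section does not say which variance it used, so both usual forms are shown: SD = √(1 − 0.67²) for a baseline-adjusted analysis and SD = √(2(1 − 0.67)) for change scores.

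| p | Effect | Power, baseline-adjusted | Power, change score |
|---|---|---|---|
| 0 | 0.25 | 88.9% | 82.8% |
| 2% | 0.245 | 87.6% | 81.3% |
| 5% | 0.2375 | 85.6% | 78.8% |
| 10% | 0.225 | 81.7% | 74.4% |

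The gap between the first row and the stated 90% is a separate matter. Here only the fall down each column counts: 1.3 to 7.2 points (baseline-adjusted) or 1.5 to 8.4 points (change score).

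**Unmasking.** The bias is p(b1 − b0). The documents give no value for b1 − b0. If it were as large as the design effect, the bias would be 0.02 × 0.25 = 0.005 to 0.10 × 0.25 = 0.025, in either direction.

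**The case against.** The strongest reply is that exposure is inferred, not documented. The video was to be released only if the trial showed no net harm, and its website was offline during the trial. No section says that anyone in these networks had seen it. The channel is one of several, beside students, parenting groups and sporting groups, and the Recruitment section does not name the film and advertising colleagues. Participant masking is already described as partial. The article also condenses a full protocol that might contain a screen.

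Most of this stands as a limit on size. It does not remove the point, because the article gives headed eligibility criteria and presents this channel as a step that reduces bias without weighing the risk it carries.

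A reader might also infer more than the documents support:

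- **That prior exposure in either arm shrinks the contrast.** It does not; exposed control men leave the expected change contrast unaltered apart from any reporting shift.
- **That baseline scores become unbalanced.** Exposure before randomisation balances in expectation.
- **That masking fails for the trial as a whole.** It fails only for the men concerned.

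**Conclusion.** The concern holds as a gap in eligibility combined with a recruitment channel that makes the gap relevant. Following the plan as written can randomise men whose T1 is not pre-exposure and who can infer their arm. The documents do not show that this happened or how often, and the 2% to 10% range is an assumption.

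Dilution alone is modest at a small share, and by itself it pulls the efficacy estimate towards no effect, so it cannot create a false benefit. The more important route is arm-dependent unmasking of a self-reported outcome, because it can act in either direction and comparing changes does not cancel it. It too scales with the exposed share. The change is worth making because it is cheap and specific, not because a large bias has been demonstrated.

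**What to change.** 1. Add an exclusion criterion for men who took part in making the video or have already seen it.
2. Apply it without disclosing the purpose. Check registrants against the cast and crew list, which the data contractor could do since it already holds identifying data. Ask the film and advertising colleagues not to forward the flyer to cast, crew or anyone shown the video. A registration question that lists videos should be avoided, since it would hint to every registrant at the aim that the Recruitment section withholds.
3. Add a prior-awareness item beside the believed-allocation question at T3, where the two groups are explained anyway. Place it after the outcome scales and word it to refer to the time before the T1 session.
4. Prespecify a sensitivity analysis of the primary outcome without men who report prior exposure, and report their number by arm.

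The T3 item has limits. It is answered after allocation, so recall may differ by arm, and men who miss T3 give no answer. It also arrives after the planned T2 analysis and so cannot inform the release decision. It supports a sensitivity analysis and does not replace the exclusion.

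The cost is a protocol and ethics amendment, a few registrants lost, one T3 item and one analysis. Recruitment was scheduled to end on 2 October 2021 and data collection at the end of November 2021. If recruitment has closed, steps 3 and 4 are what remains, provided T3 is still open.

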## Trial status

This RCT has been the Australian New Zealand Clinical Trials Registry (No. 12621001008819) [9]. Recruitment commenced on 16 August 2021 and will end on 2 October 2021. Data collection will continue until the end of November 2021.

## Data Availability

We will make available upon reasonable request the de-identified individual quantitative participant data collected during the trial and the study protocol after the publication of the trial results.

## Abbreviations

CMNI-30-SR: Conformity to Masculine Norms Inventory 30—Self-Reliance subscale
DSI-SS: Depression Symptom Inventory—Suicidality Subscale
GHSQ-Self: General Help-Seeking Questionnaire—Self
GHSQ-Other: General Help-Seeking Questionnaire—Other
HSUQ: Health Service Use Questionnaire
MDRS-7: Male Depression Risk Scale-7
PLS: Plain Language Statement
RCT: Randomised controlled trial
